#### Pre-defined subgroups

1.2.4

Pre-defined subgroup analyses will be performed for the subgroups of patients with alcoholic vs non-alcoholic etiology, for patients with biliary vs non-biliary etiology, for patients with older age (defined as age ≥65 years vs age <65 years) and the subgroups with and without vasopressor use at baseline.

Table 4 summarises the schedule of events.

**Table 4 T4:**
[figure not shown]
Schedule of events.

### Statistics

1.3

The incidences of the primary endpoint and all dichotomous secondary endpoints will be compared using the Chi-Square test or Fisher exact test as appropriate.

All comparisons of continuous endpoints within groups and between groups will be performed using *t* test or Wilcoxon-test for paired or unpaired samples as appropriate.

A p-value of *P*<.05 is considered as significant.

Missing values over time will be replaced using “last value carried forward”.

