### Aim, design and setting of the study

1.1

It is the objective of the PACIFIC-study to investigate if early administration of CytoSorb in patients with SAP substantially improves hemodynamic characteristics including vasopressor dosage and cardiac power index (CPI).

The PACIFIC-trial is designed as a prospective multi-center case-control study.

The study will be performed in intensive care units (ICU) experienced in the use of CytoSorb and capable of combined TPTD and pulse contour analysis (PCA) monitoring.

All patients will be monitored by PiCCO (Pulsion Medical systems SA, Feldkirchen, Germany) or EV-1000 (Edwards Lifesciences, Irvine, CA).

The matched controls will be recruited from patients with SAP treated in a comparable setting including TPTD-monitoring, but not treatment with CytoSorb or any other cytokine adsorbing devices.

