**Table 3 T3:**
[figure not shown]
Primary and secondary endpoints.

The primary endpoint is defined as an improvement of hemodynamics with a decrease in the vasopressor dependency index (VDI) of at least 20% within 48 h compared to the baseline measurement immediately before the onset of therapy with CytoSorbents (CytoSorb). For patients without vasopressor therapy at baseline, the primary endpoint is defined as an improvement in CPI of at least 20%.

The VDI is defined as the ratio of the inotropic score divided by mean arterial pressure (MAP):

VDI = inotropic score / MAP

The inotropic score is defined as (dopamine dose_1) + (dobutamine dose∗1) + (adrenaline dose∗100) + (noradrenaline dose∗100) + (phenylephrine dose∗100). All doses are given as μg/kg/min.

TPTD will be performed at baseline as well as after 6, 8, 12, 16, 24, 30, 32, 36, and 48 h after the initiation of blood purification.

Outcome analysis will be based on a comparison of the incidence of the primary endpoint in 30 intervention patients compared to 60 matched controls with advanced hemodynamic monitoring recruited from recent studies in SAP within the same setting and the same centers. To account for different numbers of TPTD measurements in the controls (usually 2–3 measurements within 24 h), the primary outcome analysis will be performed based on the measurements at baseline as well as after 12, 24, 36, and 48 h after the initiation of CytoSorb-therapy.

APACHE-II-score on inclusion and baseline VDI are the main criteria for matching.

Secondary analyses will include laboratory (cytokine levels) and translational endpoints (including multiplex-ELISAs of numerous anti- and pro-inflammatory cytokines/chemokines and DNA analyses).

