#### Power calculation

1.3.1

Power calculation is based on the assumption that the primary endpoint is fulfilled in 67% of the 30 patients in the intervention-group and in 33% of the 60 matched controls. This results in a statistical power of 87.8% (https://www.dssresearch.com/KnowledgeCenter/toolkitcalculators/statisticalpowercalculators.aspx).

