With regard to the complexity of numerous diagnostic and therapeutic approaches in SAP, the impact of single measures such as 2-day extracorporeal cytokine elimination should not be overestimated. Necessarily, this has to be considered for the study design, in particular for the primary endpoint and the power calculation. Therefore, we chose changes in the VDI as the primary endpoint. VDI has been repeatedly used as an endpoint in studies focused on extracorporeal cytokine and toxin elimination.^[12,18]^

Patients similar to the patients selected according to the inclusion criteria of PACIFIC have been treated by most PACIFIC study centers during the randomized controlled EAGLE-trial (https://clinicaltrials.gov/ct2/show/NCT00894907). The EAGLE-study investigates the impact of TPTD guided volume resuscitation on outcome. Half of the intended number of 182 patients of the EAGLE-study will be under hemodynamic monitoring with the PiCCO-device. Since the inclusion criteria and the clinical setting are nearly identical as for PACIFIC, data from patients from the EAGLE-study with PiCCO-monitoring will be a major source for the allocation of matched controls.

In addition to the primary endpoint and several standard secondary outcomes such as organ failures and mortality, the PACIFIC-trial will analyze several measures of inflammation at baseline and over time. The importance of pro-inflammatory cytokines in pancreatitis has been highlighted by a recent study in 84 patients with AP who were screened for known polymorphisms in TNFα, interleukin 1 (IL-1), IL-1 receptor antagonist (IL1RN), IL-6, and IL-10. The study demonstrated that the TNFα −238 AG genotype, but not the TNFα −308 SNP, was associated with organ failure (shock and/or respiratory failure) during AP.^[19,20]^ A very interesting candidate that seems to drive the pathophysiology of MOF during AP in experimental animal models is IL-6. IL-6 not only regulates the acute phase response in the liver, it can also activate a plethora of pro-inflammatory pathways, such as Stat3 and NF-kappaB.^[21]^

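### The non-randomised, matched primary comparison is fixed as an unadjusted independent-samples chi-square/Fisher test; it should be adjusted for the matching variables

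*Protocol article*

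**What the plan says.** The section on aim, design and setting describes a non-randomised study: "The PACIFIC-trial is designed as a prospective multi-center case-control study". The Outcomes section (1.2.3) bases the primary analysis on a "comparison of the incidence of the primary endpoint in 30 intervention patients compared to 60 matched controls with advanced hemodynamic monitoring" and adds that "APACHE-II-score on inclusion and baseline VDI are the main criteria for matching". The Discussion says where many controls come from: "data from patients from the EAGLE-study with PiCCO-monitoring will be a major source for the allocation of matched controls".

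The Statistics section (1.3) then fixes the test. Incidences of the primary endpoint and of all dichotomous secondary endpoints "will be compared using the Chi-Square test or Fisher exact test as appropriate". The choice left open is between two independent-samples tests. For continuous endpoints the same section allows paired or unpaired versions, but for binary endpoints it names no paired, stratified or covariate-adjusted option. The power calculation (1.3.1) assumes that "the primary endpoint is fulfilled in 67% of the 30 patients in the intervention-group and in 33% of the 60 matched controls".

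**The concern.** Randomisation does not protect this comparison, so its credibility rests on the matching and on the analysis. The stated analysis drops the matching and adjusts for nothing. This can go wrong in two opposite directions.

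- **Close matching in individual sets.** Outcomes within a set are then positively correlated. The chi-square standard error is too wide, and information is thrown away in a study with 30 treated patients.
- **Loose matching.** Any leftover difference in baseline severity is credited to, or held against, CytoSorb. An unadjusted test cannot separate the two.

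This is the only primary test, so the study's main conclusion depends on it.

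**Working it through.** **Inputs from the protocol.** 30 treated and 60 controls; response 67% and 33%; significance at 0.05 (two-sided is assumed, since sidedness is not stated and two-sided reproduces the power); matching on APACHE-II and baseline VDI.

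**Inputs not in the protocol (assumed, shown as ranges).** Within-set outcome correlation; imbalance remaining after matching; prognostic strength of the covariates; individual 1:2 sets, inferred from 30 against 60.

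**1. The plan's own figure.** Pooled rate = (30×0.67 + 60×0.33)/90 = 0.4433. Null SE = √(0.4433×0.5567×(1/30+1/60)) = 0.1111. Alternative SE = √(0.67×0.33/30 + 0.33×0.67/60) = 0.1051. Power = Φ((0.34 − 1.96×0.1111)/0.1051) = Φ(1.163) = 87.76%, which is the stated 87.8%. Exact enumeration gives 87.7% for the uncorrected chi-square and 86.2% for Fisher. The stated power is therefore correct, and it is the power of an unmatched test.

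**2. Close matching, by formula.** In a 1:2 set with within-set correlation ρ, Var(treated − mean of two controls) = pq(1 + (1+ρ)/2 − 2ρ) = 1.5pq(1−ρ). The chi-square test uses 1.5pq. Its SE is too wide by the factor 1/√(1−ρ), and the true two-sided error is 2(1 − Φ(1.96/√(1−ρ))).

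| ρ | SE too wide by | true type I error |
|---|---|---|
| 0.1 | 5% | 3.9% |
| 0.2 | 12% | 2.8% |
| 0.3 | 20% | 1.9% |

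**3. Close matching, by simulation.** 40,000 trials per scenario, 30 sets of 1:2, a normal set effect on the logit scale, marginal rates as planned. The comparator is the set-stratified Mantel-Haenszel (MH) test.

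| Within-set correlation | chi-square type I | chi-square power | MH power |
|---|---|---|---|
| 0 | 4.9% | 87.5% | 86.8% |
| 0.05 | 4.4% | 88.1% | 88.3% |
| 0.16 | 3.2% | 89.6% | 92.1% |
| 0.28 | 2.2% | 90.9% | 95.2% |
| 0.53 | 0.6% | 93.4% | 99.3% |

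MH type I error stays at 4.6–5.0%. The chi-square power does not fall below the planned level beyond simulation error.

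**4. Imbalance in a matching variable.** Simulated with no treatment effect and two covariates with log odds ratios 1.2 and 0.5 per SD (e^1.2 = 3.3), 70% of their variance being shared within sets. The treated group is shifted on the stronger covariate.

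| Shift (SD) | chi-square false positives |
|---|---|
| 0 | 3.3% |
| 0.1 | 4.1% |
| 0.3 | 7.2% |
| 0.45 | 13.5% |

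Logistic regression adjusted for both covariates stays at about 4–5.5% throughout. At zero shift its power is 94–95%, against 90% for chi-square.

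**5. Imbalance that nothing adjusts for.** With no treatment effect and 33% control response, a residual difference worth 5, 10, 15 or 20 points of response rate makes chi-square significant in 8%, 16%, 29% or 46% of trials (correlation 0). At correlation 0.28 the MH test gives 9%, 20%, 36% or 57%. A matched test alone is therefore no remedy for confounding; the covariates must enter the model.

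**The case against.** The strongest reply has five parts.

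- **Conservatism is not a validity failure.** With close matching the planned test cannot inflate false positives and it keeps its planned power. This stands: that half of the point concerns efficiency.
- **The anti-conservative half rests on assumptions.** It needs appreciable imbalance to remain in a strongly prognostic variable after matching on that same variable. At 0.1 SD the error is still below 5%. This stands as a limit on size. The direction of the risk remains, because nothing in the stated analysis guards against it.
- **Individual sets are inferred.** The article does not describe the matching algorithm, and calling these the main criteria implies others. This stands. If matching is only at group level, steps 2 and 3 fall away, but the case for covariate adjustment does not.
- **An article condenses the plan.** This does not answer the point. The choice of test is stated, and it is that choice that is questioned.
- **Conditional logistic regression with covariates would be no better.** In a separate small simulation (700–1,000 runs per scenario) it had power of 83–84% against 84–86% for chi-square and type I error of 2.3–3.3%. It overstated the log odds ratio (mean 2.1–2.2, true 1.7), and about 3% of fits failed. This stands, so it should not be the lead analysis with 30 sets.

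**Conclusion.** The point holds at moderate strength: should be fixed. The protocol commits its only primary test to an unadjusted independent-samples comparison in a non-randomised matched study. With close individual matching the test is conservative and gives up some power relative to an adjusted analysis. With remaining imbalance of 0.3 to 0.45 SD in a strong prognostic variable, false positives reach about 7.2% to 13.5%. These sizes depend on the assumed correlation, imbalance and odds ratio of 3.3 per SD, none of which the protocol gives.

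A reader might infer three stronger things that the document does not support:

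- **That the error rate is wrong whatever happens.** With little within-set correlation and no imbalance it is 4.4–4.9%.
- **That the study is underpowered, or the 87.8% miscalculated.** The figure reproduces, and positive within-set correlation does not lower it.
- **That a matched analysis, or adjustment for the two matching variables, would make the comparison free of confounding.** Controls come from other studies. Differences in source study, period or unmeasured factors would remain.

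**What to change.** In the Statistics section, make the primary analysis a logistic regression of the endpoint on treatment, adjusted for APACHE-II on inclusion and baseline VDI. If controls are matched in individual sets, use standard errors clustered on the set. With only 30 sets, a small-sample correction is advisable; the simulated figures above are for adjusted logistic regression and do not specifically assess clustered errors. Report the odds ratio and a standardised risk difference, each with a 95% CI. Keep chi-square/Fisher, and optionally a set-stratified Mantel-Haenszel test, as sensitivity analyses. State in the power section that 87.8% is the power of the unmatched test.

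Baseline vasopressor use need not be a compulsory extra covariate. By the protocol's definition VDI is zero when none of the listed agents is given, so baseline VDI largely determines it.

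The change costs wording only. Both covariates are already needed for the matching, and no extra patients are required. The price is somewhat more model dependence and room for only two or three covariates with 30 treated patients. Confounding by unmeasured factors, source study or period is not removed and should be stated as a limitation.

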Given the importance of cytokines in AP and the mode of action of CytoSorb, the PACIFIC-study will analyze cytokine and chemokine levels before and after the usage of CytoSorb adsorber. Such analysis will include multiplex-ELISAs of numerous anti- and pro-inflammatory cytokines/chemokines. In an explorative part of the study, DNA from the blood of these patients will be extracted for genetic analysis, particularly with respect to SNPs of factors of interest. All these analyses will add significant information to the PACIFIC studies.

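### Continuous, mainly secondary endpoints are tested without baseline adjustment, and before/after P values within groups cannot isolate a CytoSorb effect

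*Protocol article*

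**What the plan says.** Section 1.3 (Statistics) sets one rule for every continuous endpoint: "All comparisons of continuous endpoints within groups and between groups will be performed using" the t "test or Wilcoxon-test for paired or unpaired samples as appropriate". The same section adds that a P value "<.05 is considered as significant", with no exception for within-group tests. It names no covariate-adjusted model.

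Baselines are nevertheless available. Section 1.2.3 (Outcomes) states for hemodynamics: "TPTD will be performed at baseline as well as after 6, 8, 12, 16, 24, 30, 32, 36, and 48 h". The Discussion says that the trial "will analyze several measures of inflammation at baseline and over time", and that it "will analyze cytokine and chemokine levels before and after the usage of CytoSorb adsorber". That last statement mentions no control group.

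Baseline enters the comparison in two other ways. Section 1.2.3 makes APACHE-II at inclusion and baseline VDI the main matching criteria. It also defines the binary primary endpoint as a change of at least 20% from baseline.

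**The concern.** The comparison is not randomised: 30 treated patients are set against 60 matched controls, with an earlier trial as a major source. In that setting an unadjusted t or Wilcoxon test between groups has two weaknesses. It discards the prognostic information in the patient's own baseline, and it carries any baseline difference left after matching into the estimate.

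The within-group tests have a different problem. A paired test in treated patients asks whether values changed, not whether CytoSorb changed them. Patients enter within seven days of pain onset, a period that Section 1.2.1 describes as containing the first inflammatory peak, so some fall without the device is plausible. If such a test is reported as significant under the general P<.05 rule, it can be mistaken for evidence about the device. Cytokines are the most exposed endpoint because they bear directly on the mode of action.

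**Working it through.** **1. The plan's own figure.** Section 1.3.1 assumes that "the primary endpoint is fulfilled in 67% of the 30 patients in the intervention-group and in 33% of the 60 matched controls" and says: "This results in a statistical power of 87.8" percent.

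- Pooled rate: (30×0.67 + 60×0.33)/90 = 0.4433.
- SE under the null: √(0.4433×0.5567×(1/30+1/60)) = 0.1111.
- SE under the alternative: √(0.67×0.33/30 + 0.33×0.67/60) = 0.1051.
- Power: Φ((0.34 − 1.96×0.1111)/0.1051) = Φ(1.163) = 87.8%.

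The figure reproduces (two-sided, 5%). It concerns the binary primary endpoint, which does not use the tests at issue here.

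**2. Precision of the between-group comparison.** Let r be the correlation between baseline and follow-up, with equal SD at both times and roughly balanced baselines. Relative to comparing follow-up values (factor 1), the variance is 2(1−r) for change scores and 1−r² for baseline adjustment (ANCOVA). The ratio of ANCOVA to change score is (1+r)/2. The documents give no r, so 0.3, 0.5 and 0.7 are assumed.

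| | r=0.3 | r=0.5 | r=0.7 |
|---|---|---|---|
| Change score, 2(1−r) | 1.40 | 1.00 | 0.60 |
| ANCOVA, 1−r² | 0.91 | 0.75 | 0.51 |
| ANCOVA relative to change score | 0.65 | 0.75 | 0.85 |
| Unadjusted N with the same information, 90/(1−r²) | 99 | 120 | 176 |

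ANCOVA therefore saves 9%, 25% and 49% of the variance against follow-up values, and 35%, 25% and 15% against change scores.

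In power terms, take the effect that an unadjusted follow-up comparison of 30 and 60 patients detects with 80% power: (1.960+0.842)×√(1/30+1/60) = 0.63 SD. For the same effect:

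| | r=0.3 | r=0.5 | r=0.7 |
|---|---|---|---|
| Follow-up only | 80% | 80% | 80% |
| Change score | 65.8% | 80.0% | 95.1% |
| ANCOVA | 83.6% | 89.9% | 97.5% |

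**3. Residual imbalance.** If the groups differ by d SD at baseline, a follow-up comparison carries about r·d into the result, and a change score over-corrects by about (1−r)·d in the other direction. For r = 0.3, 0.5 and 0.7 that is 30%, 50% and 70% of d for follow-up values, and 70%, 50% and 30% of d for changes. The documents give no d. Matching on baseline VDI should keep it small for VDI; CPI and cytokines are not named as main criteria.

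**4. Within-group tests.** Suppose the device has no effect and values fall by δ SD on their own. A paired t test in 30 treated patients has noncentrality δ√30/√(2(1−r)) on 29 degrees of freedom. The table gives the chance of P<.05:

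| Assumed fall without device effect | r=0.3 | r=0.5 | r=0.7 |
|---|---|---|---|
| 0 | 5% | 5% | 5% |
| 0.3 SD | 27% | 36% | 54% |
| 0.5 SD | 61% | 75% | 93% |

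The values of δ are assumptions. What the plan does supply is the direction: it expects 33% of controls to reach a 20% hemodynamic improvement without CytoSorb. That is a responder rate, so it shows that such improvement is expected but does not fix an average fall.

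**The case against.** A reader might infer that the trial's main result is compromised. It is not. The primary endpoint is defined against each patient's own baseline and is compared between groups, so improvement without the device is met by a control group.

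A reader might also infer that the plan intends to credit a natural decline to CytoSorb. No sentence says that efficacy will be concluded from a within-group test, and cytokines are placed among the secondary analyses. Whether controls have cytokine samples cannot be judged from the article. What stands is narrower: the plan attaches a significance rule to tests that cannot answer the device question, and does not confine them to description.

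On size, quoting only the saving against follow-up values would overstate the loss, because Section 1.3 does not say whether follow-up values or changes are compared. At r=0.7 the saving is 49% against the former but 15% against the latter. The factor 1−r² also presumes near-balanced baselines, and imbalance erodes part of the gain.

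Matching is a fair answer on bias for VDI. It does not answer the precision point, because an unpaired test makes no use of it. An ordinary paired test, for its part, does not directly accommodate two controls per case.

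In non-randomised groups ANCOVA is not uniformly less biased than change scores, and no adjustment removes unmeasured confounding. That limits what the remedy can promise.

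Finally, modelling detail is often left to a separate analysis plan. Here, however, the article does not stay silent: it prescribes the tests for all continuous comparisons.

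**Conclusion.** The point holds for continuous, mainly secondary endpoints, as a correctable weakness in a stated method.

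- **Between groups:** the prescribed tests give up 9–49% of variance against an adjusted comparison if follow-up values are compared, and 15–35% if changes are compared, for an assumed r of 0.3 to 0.7. They leave residual imbalance uncorrected, chiefly for CPI and cytokines.
- **Within groups:** P values do not separate a device effect from improvement that would occur anyway. With an assumed fall of 0.5 SD and no device effect, 61–93% of such tests in 30 patients would be significant. This matters most for cytokines.
- **Not affected:** the binary primary analysis and its 87.8% power.

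**What to change.** Amend Section 1.3 along these lines:

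- For each continuous endpoint measured in both groups, make the main comparison a between-group model adjusted for that endpoint's own baseline and APACHE-II, and accounting for the matched sets. For repeated values use a mixed model with group, time and their interaction. The times of 12, 24, 36 and 48 h, already chosen in Section 1.2.3 to suit the controls, are the natural ones.
- Analyse VDI untransformed or by a rank-based method. VDI is the inotropic score divided by MAP, so it is zero in a patient on no catecholamine, and a plain log is then undefined. Section 1.2.3 expects patients without vasopressors at baseline.
- Report within-group changes with estimates and intervals, without significance claims.
- If controls have no cytokine samples, label the cytokine results as uncontrolled.

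The cost is a change of wording and slightly more modelling work; for endpoints measured in both groups no new data are needed. Because the groups are not randomised, residual confounding remains after adjustment, and the report should say so.

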## Background

1

Acute pancreatitis (AP) is an acute inflammatory process of the pancreas.^[1–4]^ In about 90% of patients, AP has a mild course with inflammation localized to the pancreatic gland. Mild AP has a mortality rate below 1%.^[1]^ The remaining 10% of patients develop severe AP (SAP) involving extra-pancreatic tissues and other organ systems. The outcome of SAP is closely related to the development of systemic inflammatory response syndrome (SIRS) and consecutive multiple organ failures (MOF). The mortality of SAP is around 42%.^[5]^

*Diagnosis* of AP is easily established based on the presence of at least 2 of the 3 criteria of typical epigastric pain with radiation to the back, at least 3-fold elevation of serum lipase or amylase, and evidence of AP on abdominal ultrasound or computed tomography (CT). By contrast, *therapy* for SAP is cumbersome and limited due to the lack of causative therapies apart from the removal of bile duct stones. Consequently, the therapy for SAP is predominantly symptomatic. Optimized fluid resuscitation is the cornerstone of these symptomatic therapeutic approaches, since early volume depletion and hemo-concentration have been repeatedly associated with poor outcome. In addition, early goal-directed resuscitation based on transpulmonary thermodilution (TPTD) might potentially improve outcome in SAP.^[4,6,7]^

Severity and mortality of AP are 2-peaked, with an early peak due to overwhelming SIRS and a second peak after 2 to 4 weeks, predominantly due to septic complications. With regard to the marked inflammatory response (“cytokine storm”) several attempts to prevent or limit inflammation have been investigated. However, none of the medical concepts including antioxidants,^[8]^ platelet-activating antagonists,^[9]^ antibodies against mediators of inflammation such as tumor necrosis factor alpha, or non-steroidal anti-inflammatory drugs have been shown to improve outcome in large clinical trials. This might be related to the protracted intervention aimed at limiting SIRS in a fulminant disease with already established “cytokine storm”. In addition to the delayed onset of action of medical immune-modulators, these drugs also carry the risk of side-effects, and may further impair organ function.

In this scenario, blood-purification with hemofiltration and/or hemo-adsorption with immediate elimination of cytokines may be a promising alternative.^[10]^

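### As written, a patient who reaches a 20% improvement and then dies before 48 h counts as a responder on the primary endpoint

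*Protocol article*

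**What the plan says.** Section 1.2.3 (Outcomes) defines the primary endpoint as a "decrease in the vasopressor dependency index (VDI) of at least 20% within 48 h compared to the baseline measurement". For patients without vasopressors at baseline, "the primary endpoint is defined as an improvement in CPI of at least 20" per cent. The primary analysis uses "the measurements at baseline as well as after 12, 24, 36, and 48 h" of CytoSorb therapy. It does not say whether the improvement must be present at 48 h or whether any one of these measurements is enough.

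Section 1.3 (Statistics) gives a single missing-data rule: "Missing values over time will be replaced using" last value carried forward. It does not separate values missing because the patient died from values missing for other reasons.

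On the risk of death, section 1 (Background) says "The mortality of SAP is around 42" per cent and "Severity and mortality of AP are 2-peaked, with an early peak due to overwhelming SIRS". Section 1.2.1 restricts enrolment to the first 7 days after the onset of pain. Section 1.4 has patients followed to discharge or death. The Discussion lists mortality among the secondary outcomes. The visible text does not say how a death before 48 h is classed on the primary endpoint.

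**The concern.** Haemodynamic response is meant to stand for benefit. Death within the 48 h window is the worst result a patient can have in that window, yet the two stated rules together can record it as a success. This is not a detail merely left out of a condensed article. The article does state a rule, and the rule gives the wrong answer for a patient who improves and then dies.

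The comparison is at stake as well as the meaning of the endpoint. The groups are not randomised. Controls come from earlier studies, usually with 2 to 3 measurements within 24 h, while treated patients follow a denser prospective schedule. Restricting the primary analysis to a 12-hourly grid narrows that difference but does not remove it. The last value recorded before a death, and hence the status that the patient is given, may be captured differently in the two groups.

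**Working it through.** **1. Do the rules produce the result?** Take two patients who both improve by at least 20% at 12 h.

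| Patient | Any time point qualifies | Status at 48 h required |
|---|---|---|
| A: improved at 12 h, dies at 20 h | Responder from the observed 12 h value | Responder: the 12 h value is carried to 24, 36 and 48 h |
| B: improved at 12 h, back to baseline or worse at 24 h, dies at 30 h | Responder from the observed 12 h value | Non-responder: the worse 24 h value is carried forward |

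Patient A is a responder on both readings. In the first column carrying forward plays no part and the endpoint wording is the cause. In the second column carrying forward is the cause. Patient B shows that the choice of reading changes how many deaths are affected.

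**2. The protocol's own power figure.** Inputs from section 1.3.1: p1 = 0.67 with n1 = 30, and p2 = 0.33 with n2 = 60. The significance level of 0.05 is from section 1.3; two-sided is assumed because sidedness is not stated.

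Power = Φ{[(p1 − p2) − 1.96·SE0] / SE1}, where
- pooled rate = (20.1 + 19.8)/90 = 0.4433
- SE0 = √[0.4433 × 0.5567 × (1/30 + 1/60)] = 0.1111
- SE1 = √[0.67 × 0.33/30 + 0.33 × 0.67/60] = 0.1051
- Power = Φ[(0.34 − 0.2177)/0.1051] = Φ(1.163) = 87.8%

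This matches the stated 87.8%.

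**3. Size per patient.** One treated patient is 1/30 = 3.3 percentage points. The documents give no 48 h death rate, so the numbers reclassified below are assumptions. They suppose that the planning rates count such deaths as responders, and then move them to non-response using the same formula.

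| Reclassified, treated | Reclassified, controls | Rates | Power |
|---|---|---|---|
| 0 | 0 | 67.0% vs 33.0% | 87.8% |
| 1 of 30 | 0 | 63.7% vs 33.0% | 79.9% |
| 2 of 30 | 0 | 60.3% vs 33.0% | 70.1% |
| 3 of 30 | 0 | 57.0% vs 33.0% | 58.9% |
| 4 of 30 | 0 | 53.7% vs 33.0% | 47.1% |
| 1 of 30 | 2 of 60 | 63.7% vs 29.7% | 88.0% |
| 3 of 30 | 6 of 60 | 57.0% vs 23.0% | 89.4% |
| 0 | 2 of 60 | 67.0% vs 29.7% | 93.4% |

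**4. Effect on an observed result.** Near the planning rates the counts are 20/30 and 20/60. The uncorrected chi-square is 90 × (20×40 − 10×20)² / (30×60×40×50) = 9.0, p=0.003. Moving treated patients only, against 20/60:

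| Treated responders | Chi-square p | Fisher p |
|---|---|---|
| 20/30 | 0.003 | 0.004 |
| 19/30 | 0.007 | 0.012 |
| 18/30 | 0.016 | 0.023 |
| 17/30 | 0.034 | 0.042 |
| 16/30 | 0.068 | 0.109 |

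From the planned result, the fourth reclassification is the one that crosses 0.05.

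**The case against.** The strongest reply has four parts.

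- **Carrying forward may be innocent.** If any time point within 48 h qualifies, the observed value alone makes the patient a responder, and restricting carrying forward to survivors changes nothing. This stands. It is why the point covers the endpoint wording and the missing-data rule together.
- **Few patients may be affected.** A reader might multiply the 42% mortality, or some assumed 48 h death rate, by the group sizes and treat every early death as misclassified. The documents do not support that. The 42% is overall mortality in severe disease, and the early peak is not dated to 48 h from the start of treatment; the article only contrasts it with a second peak at 2 to 4 weeks. Patients deteriorating towards death will often have a rising VDI, since VDI is inotropic score divided by MAP, and would already be non-responders. Only deaths after a qualifying value count.
- **No direction of bias is shown.** Equal shares in the two groups leave power about unchanged, and an excess among controls would work against the device. This stands.
- **A rule may exist elsewhere.** Table 3, which holds the endpoints, is not shown, and a condensed article may leave the handling of death to a fuller document. This stands in part: if such a rule exists, the unqualified sentence in section 1.3 conflicts with it and needs the exception.

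A reader might also infer that vasopressors stopped under a decision to limit care would give a VDI of 0 and count as full improvement. The formula allows a VDI of 0, but the visible text says nothing about limitation of care, and the case would need a scheduled measurement after the stop. It is not part of this point.

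**Conclusion.** The point holds in a limited form. On either reading of the 48 h window, the stated rules make a responder of a patient whose last scheduled value before an early death met the 20% threshold. If any time point qualifies, a patient who had already worsened again is included too. The number is unknown and may be small.

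A reader might conclude that one misclassified death can overturn the trial. That is true only at the boundary between 17/30 and 16/30 against 20/60 (p=0.034 and p=0.068). From the planned result it takes four treated patients with none among controls. Even with equal shares, where the comparison is hardly affected, deaths would still be reported as haemodynamic successes.

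This rests on the visible text (Table 3 is not shown), on assumed numbers of affected patients, and on a two-sided 5% test. It should be fixed, because the rule decides who counts as a success on the primary endpoint, but the documents do not show that it would change the trial's conclusion.

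**What to change.** Make three changes in sections 1.2.3 and 1.3:

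1. State that death before 48 h is non-response on the primary endpoint, whatever the earlier VDI or CPI, in treated patients and controls alike.
2. Limit last value carried forward to patients alive at the time point concerned.
3. State whether the 20% improvement must be present at 48 h or at any of the 12, 24, 36 and 48 h measurements.

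The first change corrects patient A and patient B on either reading. The third is needed because the reading also affects survivors whose improvement does not last.

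The cost is a few sentences. No new data are needed for the treated patients, who are followed to discharge or death; for controls, the date and time of any early death must be taken from the source studies. Response rates may fall slightly in both groups.
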